### Sample Size

The target sample size for this trial is 234 participants from at least 47 schools. This calculation is conservatively based on the participation of an average of 5 educators per school and an intraclass correlation of 0.07, which yields a design effect of 1.28. To detect a standardized effect size of 0.50, (a minimum of a moderate effect size is required to warrant future value and benefit of the program) with 80% power and α=.05 (2-tailed), an individually randomized trial would require 64 participants per arm. This number is inflated by the design effect to 82 to allow for clustering, with the recruitment increased to conservatively allow for attrition of up to 30%. This yields a minimum of 117 participants per arm.

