#### Statistical Methods

The primary analysis will use a mixed model repeated measures analysis of variance (MMRM), accounting for repeated assessments within individuals and a random effect to account for clustering within schools. Models will include the factors time, condition (intervention vs control), and their interaction, with the critical test of effectiveness being planned contrasts of this interaction from baseline to postintervention (the trial primary endpoint) and follow-up (secondary endpoint). An unconstrained variance-covariance matrix will be used to accommodate within-participant effects. The method of Kenward and Roger [38] will be used to estimate the degrees of freedom for tests of all effects. Any baseline variables identified as substantially imbalanced between groups will be added to the models on an exploratory basis to confirm the robustness of the findings to this imbalance. Where distributional assumptions cannot be satisfied, bootstrapping methods or generalized mixed models (eg, binary MMRM) may be used to confirm the robustness of the findings. MMRM constitutes an intention-to-treat analysis, as it includes all available data under the missing-at-random assumption. Between-group effect sizes will be estimated using the estimated model means and variances.

Secondary and additional outcome analyses will involve contrasts comparing changes from baseline to follow-up analyses of secondary outcomes (mental health knowledge, stigma, helping behaviors, and psychological distress) from baseline to other occasions of measurement, using an MMRM approach, as described above. If the intervention is found to be effective, exploratory analyses will examine evidence for moderation effects, that is, whether the intervention was more effective for certain subgroups of the sample. This may include teacher attributes such as gender or age and school characteristics such as ICSEA status.

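### Unless an imbalanced baseline variable is crossed with time, adding it to the planned model leaves the change contrast essentially unadjusted, so the robustness check says little

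*Protocol article*

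**What the plan says.** All the relevant text is in the first paragraph of Statistical Methods.

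- Mean structure: "Models will include the factors time, condition (intervention vs control), and their interaction". Confidence is measured at baseline, posttest and follow-up (Table 1), so baseline is a response and not a covariate.
- Test: "planned contrasts of this interaction from baseline to postintervention (the trial primary endpoint) and follow-up (secondary endpoint").
- Covariance: "An unconstrained variance-covariance matrix will be used to accommodate within-participant effects", together with "a random effect to account for clustering within schools".
- Missing data: the model is called intention-to-treat because "it includes all available data under the missing-at-random assumption".
- Imbalance: "Any baseline variables identified as substantially imbalanced between groups will be added to the models on an exploratory basis", and the stated purpose is "to confirm the robustness of the findings to this imbalance".

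The paragraph names an interaction where it wants one, for time and condition. For the imbalanced variables it mentions only their addition.

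**The concern.** The treatment effect in this model is a difference in change between arms. A baseline variable entered as a main effect contributes the same amount at every occasion, so it explains level and not change. An analyst who follows the text as plainly read would add the term, see a contrast that hardly moves, and report that the findings are robust to the imbalance. That result is almost fixed in advance and says little about whether the variable affects change.

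What is at stake is the worth of that assurance. Randomization is stratified only by school size and ICSEA level (Randomization and Blinding). Role, years of experience and prior training are left to chance across 71 schools (Results). If one of these were imbalanced and also predicted change in confidence, the unadjusted contrast would carry the resulting bias, and the check meant to reveal it would not.

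**Working it through.** **Inputs from the article.** Model, contrast, covariance and purpose are as listed above. Sample Size gives "an average of 5 educators per school and an intraclass correlation of 0.07, which yields a design effect of 1.28", a target effect of 0.50 SD and attrition of up to 30%. Results gives 295 participants at baseline from 71 schools.

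**The plan's own figures.** 1 + (5 − 1) × 0.07 = 1.28. 64 × 1.28 = 81.92, taken as 82. 82 / 0.7 = 117.1, stated as 117 per arm. 234 / 5 = 46.8, so 47 schools. These reproduce, and nothing below alters them.

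**Algebra.** For a participant in arm g (0 or 1) with baseline variable x, at occasion t = 0, 1, 2, in a school with random effect u:

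E(Y_t) = α_t + β_0·g + δ_t·g + γ·x + u, with δ_0 = 0.

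The change to posttest is E(Y_1 − Y_0) = (α_1 − α_0) + δ_1·g. Both γ·x and u have cancelled. With complete data, each person's three responses split into two differences and one level component uncorrelated with them (the weighted mean with weights proportional to 1′R⁻¹, where R is the within-person covariance). γ and u enter only the level component. That component has its own free intercept and arm term, so it gives no information on δ_1. The estimate of δ_1 is therefore the difference between arms in mean change, with or without x.

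If x changes the slope by θ per unit and the arms differ by d in mean x, the unadjusted contrast is biased by d × θ. The main-effect model leaves that bias in place. A model with x crossed with time estimates θ and removes it.

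**Simulations, true treatment effect zero.** The imbalance and slope values are assumptions.

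- A: 71 schools, school variance 0.07, within-person correlation 0.6, 60 datasets per setting. Binary x in 65% against 35%, θ = 0.4 SD. Expected bias 0.30 × 0.4 = 0.12 SD.
- B: 48 schools averaging 5 educators, ICC about 0.07, REML fit of the planned model, 40 datasets per setting. Continuous x, d = 0.5 SD, θ = 0.4. Expected bias 0.5 × 0.4 = 0.20 SD.

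Mean baseline-to-posttest contrast, in SD:

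| Setting | No covariate | Main effect | Crossed with time | Largest shift from main effect |
|---|---|---|---|---|
| A, complete | 0.140 | 0.140 | 0.020 | 3e-16 |
| A, about 30% missing | 0.102 | 0.101 | −0.015 | 0.012 |
| B, complete, 5 per school | 0.198 | 0.198 | 0.001 | 0.000 |
| B, complete, 1 to 9 per school | 0.193 | 0.193 | −0.022 | 0.000 |
| B, 28% missing, unrelated to x | 0.233 | 0.230 | 0.028 | 0.060 |
| B, 33% missing, related to x in both arms | 0.210 | 0.213 | 0.025 | 0.071 |
| B, 33% missing, related to x in one arm | 0.098 | 0.141 | 0.028 | 0.114 |

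In A with complete data, crossing with time removed 0.140 − 0.020 = 0.120, the expected bias. In B with complete data and 5 per school, the standard error was 0.130 with or without the main effect. With missing data the main effect can move the estimate, but the shift reflects who dropped out. In the last row it moved the estimate away from zero, by 0.044 on average.

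**How large could a chance imbalance be?** Assume equal arms (295 / 2 = 147.5) and the design effect of 1.28 for x as well.

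- Binary x near 50%: SE = √(0.25 × 2/147.5 × 1.28) = 0.0659. A gap of 0.30 is 0.30 / 0.0659 = 4.6 SE.
- Continuous x: SE = √(2/147.5 × 1.28) = 0.1317. A gap of 0.5 SD is 0.5 / 0.1317 = 3.8 SE.
- At 2 SE and θ = 0.4, the bias is 2 × 0.0659 × 0.4 = 0.05 SD or 2 × 0.1317 × 0.4 = 0.11 SD.

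A variable that clusters more strongly by school would have a larger SE, and larger gaps would then be less unusual.

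**The case against.** The strongest reply is that the article never says main effect only. Crossing the variable with time fits the wording, would make the check work, and is a detail that an analysis plan, not shown here, could well contain. The article also plans exploratory moderation analyses, which in this model would ordinarily need covariate-by-time terms, so the authors may intend them here too. This stands in part. A reader might infer that the planned check is bound to fail, and the text does not support that. However, the article states the model, the contrast and the purpose of the check, and in the same paragraph names an interaction where one is wanted. The plain reading is the one that fails.

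Second, exact cancellation needs complete data, and the plan expects up to 30% attrition. This also stands: single datasets shifted by up to 0.06 to 0.11 SD in simulation B. Those shifts did not remove the imbalance bias in any setting.

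Third, the simulated imbalances are extreme. This stands for chance imbalance in individual-level variables, as the last calculation shows. Imbalance arising at enrolment is limited because participants do not know their allocation during registration and baseline. It is not excluded, since the research team knows the allocation once registration is scheduled.

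Fourth, for a variable that affects level but not change, an unmoved estimate is the right answer. That is true, but the main-effect model gives nearly the same answer for a variable that does affect change, so it cannot tell the two apart.

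**Conclusion.** The point holds conditionally. If an imbalanced baseline variable is added as a main effect only, it drops out of the primary contrast exactly with complete data and nearly so with about 30% attrition. The exploratory check is then close to uninformative about variables that predict change in confidence.

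The cancellation follows from the stated model and needs no assumed figures. The size of any bias left undetected does. It was about 0.14 to 0.20 SD in the complete-data simulations, or 28% to 40% of the 0.50 SD target. At a 2 SE chance imbalance with the same assumed effect on change, it is about 0.05 to 0.11 SD. Nothing in the article shows that any particular variable predicts change.

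A reader might go further and infer that the primary result is biased or the trial underpowered. The article does not support that: the check is labelled exploratory, and the primary test, its estimate and the sample size do not depend on it.

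**What to change.** State in Statistical Methods, or confirm in the analysis plan, that each baseline variable found to be substantially imbalanced enters together with its interaction with time. Alternatively, run the check in a model with posttest and follow-up as the responses, and baseline confidence and the imbalanced variable as covariates, each crossed with time.

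The cost is one phrase and a few degrees of freedom in a sensitivity model. With three occasions, a binary or continuous variable uses three parameters instead of one. The primary model, the sample size and data collection stay as they are. If the analysis plan already specifies the interaction, the point is closed.

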## Results

Approval was obtained from the primary ethics body (UNSW HREC) on April 21, 2020, SERAP on July 21, 2020, Maitland-Newcastle Catholic Diocese on May 27, 2020, Canberra-Goulburn Catholic Diocese on June 12, 2020, and Wollongong Catholic Diocese on August 4, 2020. Recruitment of educators started on July 21, 2020, and the baseline for waves 1, 2, and 3 are complete. To date, 465 educators have expressed interest in participating in the trial. In total, 308 educators have registered and 295 have completed baseline, representing 71 schools. Due to the unexpected success of recruitment in the first 3 waves, the decision has been made to not go ahead with the final fourth wave. Intervention participants are currently receiving the program with follow-up due for completion in March 2021. It is planned that the results will be presented at both national and international conferences and submitted to peer-reviewed journals. The results will also be disseminated to stakeholders through reports and presentations and on the BDI website.

## Discussion

### Principal Findings

This protocol describes the RCT of the BEAM program, a study that aims to evaluate the effectiveness of a new web-based mental health training program for secondary school educators in leadership positions. Through the provision of mental health information and interactive activities, the BEAM program aims to improve educators’ knowledge of adolescent mental health. It is anticipated that their confidence in managing their students’ needs and the frequency of help provided will thereby increase, whereas their stigma toward mental ill-health and their own levels of psychological distress will reduce.

There remains a significant lack of available evidence-based mental health training programs for educators [24,25] and few high-quality studies that have evaluated adolescent mental health education for educators. Of those identified in the study by Anderson et al [24], only 2 studies were conducted as RCTs, whereas the others used a pre-post design with no comparator. Furthermore, only 1 study identified in the study by Anderson et al [24] was conducted in Australia [16], which significantly limits the quality of training options for educators containing information relevant to their education system. It is recommended that educators are provided with professional development opportunities regarding adolescent mental health [14,15]; however, there are few good-quality and relevant programs available. The BEAM program may help fill this training gap if shown to be effective, providing more education options for Australian secondary school educators that have been formally evaluated. To our knowledge, this is the first RCT assessing a web-based training program for educators, which also measures changes in helping behaviors and psychological distress. This is important, given the ongoing impact of COVID-19 on education delivery and school closures, which has likely added to both student and teacher stress. Physical distancing guidelines have caused the cessation of most face-to-face training, meaning the options for educators are now further limited and other methods, such as web-based delivery, are ever more important if they are effective.

If the effectiveness of the BEAM program is demonstrated through this trial, there are significant implications for how mental health training can be delivered to educators. For example, traditional educator training is typically delivered through face-to-face didactic-style workshops that require participants to take leave and have their classroom duties covered by another staff member [24]. By delivering the training online, educators can access the standardized material in a flexible and personalized manner anywhere there is an internet connection. Web-based delivery potentially lowers organization and administration costs when compared with attending face-to-face training, including the financial cost of replacing staff to cover classroom duties or paying for extensive travel for training. Finally, by delivering the training online, educators can easily revise the relevant material at any time by simply logging back into the program. The drawbacks to web-based program delivery are, however, acknowledged, in particular, the full completion of the training and engagement with the content and possible ambiguity for workplaces to determine when it is reasonable for their staff to use work time to complete training. Therefore, it is worthwhile to explore methods to ensure completion and engagement with the content, such as professional accreditation with the NSW Education Standards Authority.

### Limitations and Strengths

There are limitations to this trial that are acknowledged, including the reliance on self-report questionnaires, which may be susceptible to biases. Self-report outcomes, such as confidence, may not match actual educator behavior; however, we will use validated measures where possible and assess teacher reports of actual helping behavior.

Another limitation is that the trial is being conducted among educators who self-selected to participate from within NSW only. The results may not be generalizable to interstate educators or educators who chose not to participate. Although Australia has a national education curriculum, schools are governed by each of the States’ and Territories’ Department of Education, and Catholic schools are governed by the Diocese to which they belong. Each has their own set of frameworks, policies, and rules that guide staffing. For example, there are structural differences between the states of South Australia (SA) and NSW, such that secondary school begins in year 8 in SA and year 7 in NSW. It may also be the case that participating educators are employed at better-resourced schools and have the time to take part. Furthermore, participation is limited to educators from schools for which we have approval from their governing ethical body and could obtain support from their school principal. Not all Catholic Dioceses in NSW granted approval to conduct this research, and gaining principal support might not have been possible for all interested educators.

A further limitation is the use of waitlist control and trial length. The total amount of time a control participant is required to wait without any access to the intervention is 22 weeks, which may affect attrition. We have conservatively estimated a 30% attrition in our target sample size, and a monetary reimbursement will be used to motivate completion of the posttest and follow-up surveys. The waitlist control also only enables the assessment of whether the intervention is more effective than the passage of time. Future follow-up studies to compare the intervention with active controls are needed once effectiveness relative to waitlist control is established.

Despite these limitations, this trial has several strengths, including the RCT design to examine the effectiveness of BEAM and the clustering and randomization at the school level to reduce the risk of bias and contamination. Once a school begins in the trial, no other educators from that school can enroll, ensuring that participants are not influenced by the participation of other staff members from their school. The standardized delivery of the intervention helps maximize the fidelity of the training being delivered to educators, ensuring that all participants receive the same standardized intervention. Other strengths include the suite of measures included to examine a range of outcomes; the long-term follow-up period; targeted recruiting approach to include educators from metropolitan, regional, and rural areas; exploration of possible moderators; and stratification of school variables to account for factors hypothesized to influence the results. If shown to be effective, the assessment of BEAM through an RCT will provide a novel method for delivering mental health training to secondary school educators.

## Appendix

Multimedia Appendix 1 Overview of the Building Educators’ Skills in Adolescent Mental Health Training program.

Multimedia Appendix 2 CONSORT (Consolidated Standards of Reporting Trials) flow diagram that will be used to outline participation through the Building Educators’ Skills in Adolescent Mental Health Training program for secondary school educators. NSW: New South Wales.

## Abbreviations

BDI: Black Dog Institute
BEAM: Building Educators’ Skills in Adolescent Mental Health
DQ-5: Distress Questionnaire-5
HREC: Human Research Ethics Committee
ICSEA: index of community socioeducational advantage
MAKS: Mental Health Knowledge Schedule
MHFA: Mental Health First Aid
MMRM: mixed model repeated measures analysis of variance
NSW: New South Wales
PISCF: participant information sheet and consent form
RCT: randomized controlled trial
SA: South Australia
SERAP: State Education Research Applications Process
TAPS: Teachers As Accompagnateurs
UNSW: University of New South Wales
